### Data Entry and Quality Control

Embryological laboratory data and treatment-related information including Controlled Ovarian Hyperstimulation (COH) and baseline characteristics will be collected on the day of embryo freezing. On the other hand, data on the FET cycle will be collected on the day of frozen embryo transfer. According to the study protocol, participants’ follow-up data will include that from enrollment and one year onwards. Moreover, patients’ information forms will be retrieved for data entry. Investigators will also be required to ascertain the data accuracy levels (first and second levels), as both levels will include data validation and monitoring, which will be conducted regularly throughout the study by the Data Monitoring Committee (DMC). Data will also be backed up to another computer within the same physical location as the server, on a daily basis.

### Statistical Analysis and Sample Size Calculations

#### Estimation of Sample Size

The PASS software version 11.0 (NCSS, LLC. Kaysville, Utah, USA.) will be used to calculate the sample sizes for both groups. Notably, the ongoing pregnancy rate per FET was about 30% based on data from our reproductive center, at the time of the trial design. The calculation revealed that 329 women were to be included in each trial group to provide an 80% power to detect a minimally important absolute difference of 10% points between the immediate and delayed groups for the primary outcome of ongoing pregnancy (40 *vs* 30%) at a two­sided *α* level of 0.05. However, the trial plans to include 732 women, with 366 participants in each arm in order to account for an expected 10% loss to follow-up.

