## Highlights

The present study is the first randomized controlled trial to attempt to accumulate significant clinical evidence and draw conclusions with regard to the ideal time to conduct FET after a failed fresh embryo transfer cycle.The current protocol includes participants aged 21–44 years, undergoing their first FET after the fixed GnRH antagonist protocol with standard Controlled Ovarian Stimulation (COS) in the IVF/ICSI procedure. The results obtained will therefore be able to reflect the situation in a majority of women in the infertile population.However, it will be impossible to blind the allocation of intervention measures to the participants, physicians, and researchers.The sample size calculation in the current study may also not be able to detect smaller differences in the ongoing pregnancy rates of 10% between the immediate and delayed groups.

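### 329 per arm does not follow from 40% vs 30% at two-sided 0.05 and 80% power: those inputs need 354 to 356, and 329 gives about 77% power

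*Protocol article*

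**What the plan says.** All inputs stand in one paragraph of the protocol article, under Estimation of Sample Size.

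- Reference rate: "the ongoing pregnancy rate per FET was about 30% based on data from our reproductive center".
- Target: a "minimally important absolute difference of 10% points between the immediate and delayed groups", "for the primary outcome of ongoing pregnancy (40 *vs* 30"%).
- Error rates: a two-"sided *α* level of 0.05", with the size chosen "to provide an 80% power to detect" that difference.
- Result: "The calculation revealed that 329 women were to be included in each trial group to provide an 80% power to detect" it.
- Loss allowance: 732 women in total, "366 participants in each arm in order to account for an expected 10% loss to follow-up".

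The title, the abstract and the Study Design section all call the trial non-inferiority. The sample-size section names no non-inferiority margin and does not say which arm is expected to have 40%. The Highlights also speak of detecting differences: the sample size "may also not be able to detect smaller differences in the ongoing pregnancy rates of 10"%.

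**The concern.** The paragraph gives everything needed for a two-proportion calculation, so the result should be reproducible, and it is not. The gap is larger than rounding or the choice of formula explains.

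Two things are at stake. The power claim is too high for the comparison it is attached to. The mismatch also leaves unclear which hypothesis the trial was sized for: the words describe detecting a difference, the declared design is non-inferiority, and the number fits the second better than the first. A reader who wants to know what 366 women per arm can show gets different answers from the words and from the number.

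**Working it through.** **Inputs.** From Estimation of Sample Size: rates 0.40 and 0.30, difference 0.10, two-sided alpha 0.05 (z = 1.960), power 80% (z = 0.8416), equal arms, 329 per arm, 10% loss. (1.960 + 0.8416)² = 7.849.

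**1. The stated calculation: 40% vs 30%, two-sided.**

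- Unpooled: n = 7.849 × (0.40×0.60 + 0.30×0.70) / 0.10² = 7.849 × 0.45 / 0.01 = 353.2, so 354.
- Pooled (mean rate 0.35): n = [1.960 × √(2×0.35×0.65) + 0.8416 × √0.45]² / 0.01 = [1.960 × 0.6745 + 0.8416 × 0.6708]² / 0.01 = 355.9, so 356.
- Arcsine: 355.4, so 356.
- Pooled with continuity correction: 376.

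Other readings of the same sentence do not give 329 either:

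| Variant | n per arm |
|---|---|
| 40 vs 30%, one-sided 0.05 | 281 |
| Same, with continuity correction | 300 |
| 20 vs 30%, two-sided 0.05 | 294 |
| Same, with continuity correction | 313 |
| 40 vs 30%, two-sided 0.05, 90% power | 477 |
| 40 vs 30%, one-sided 0.05, 90% power | 388 |

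**2. Power at the stated size, 40% vs 30%, two-sided 0.05.**

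- Pooled, n = 329: Φ[(0.10×√329 − 1.960×0.6745) / 0.6708] = Φ(0.733) = 76.8%.
- Unpooled, n = 329: Φ[0.10×√(329/0.45) − 1.960] = Φ(0.744) = 77.2%.
- Exact binomial power of the chi-square test, n = 329: 76.9%.
- Pooled, n = 366 with no loss: Φ(0.881) = 81.1%.

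**3. The loss allowance.** 329 / 0.9 = 365.6, so 366 per arm and 732 in total. This step reproduces. The discrepancy therefore lies in the 329 or in its description.

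**4. A non-inferiority calculation.** Assumed here, because the section does not state them as such: 30% in both arms, a margin of 10 points, one-sided alpha 0.025. Power is 80%.

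- Unpooled: n = 7.849 × (2×0.30×0.70) / 0.10² = 7.849 × 0.42 / 0.01 = 329.65, so 330.
- Farrington-Manning score formula: under a true difference of −10 points, the constrained rates are about 0.2547 and 0.3547, and the square root of their summed variances is 0.6471. Then n = [1.960 × 0.6471 + 0.8416 × √0.42]² / 0.01 = 328.93, so 329.
- Unpooled power at 329: Φ[0.10×√(329/0.42) − 1.960] = 79.9%.

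**5. Which formula fits 366 enrolled.** The score-based 329 leads to 366, as in step 3. The unpooled 330 does not: 330 / 0.9 = 366.7, so 367 per arm (734 in total), and 366 × 0.9 = 329.4 is below 330.

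**The case against.** The best defence is that the shortfall is small. About 77% against 80% is three points, the 30% rate is itself only approximate, and 366 per arm would give 81%. The first two points stand and limit the practical importance. The third fails on the plan's own terms: the extra women are there to absorb a 10% loss, and after that loss about 329 remain.

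A reader might go further and infer that 329 is plainly a non-inferiority number wrongly labelled. The documents do not support that much. The section gives no margin, no one-sided 0.025 and no assumption of equal rates, and it calls the 10 points a difference to detect. The agreement is to the patient with the score formula and within one patient with the unpooled formula. That makes this origin probable, but the PASS output is not shown.

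A reader might also infer that the trial must enrol more women. For 40 vs 30% at 80% power it would need 356 / 0.9 = 396 per arm, against 366. That follows only if detecting 40 vs 30% is the real objective, which the declared non-inferiority design makes doubtful.

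Two neighbouring statements are not further errors. The loss inflation is right, and the Highlights only repeat the language of detecting differences.

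Finally, a number reconstructed backwards does not justify a margin. Ten points on a 30% rate is a third of that rate (10/30), and accepting such a loss needs the sponsor's own justification.

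**Conclusion.** The point holds as a failure to reproduce. With the stated inputs the requirement is 354 (unpooled) or 356 (pooled) per arm, about 8% above 329 (354/329 = 1.076; 356/329 = 1.082). Power at 329 evaluable per arm is 76.8% to 77.2%, not 80%. This rests only on figures in the sample-size section and standard two-proportion formulas.

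That 329 came from a non-inferiority calculation is probable but not established. It rests on three assumptions: a 10-point margin, one-sided alpha 0.025 and 30% in both arms.

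The power deficit is modest. The correction matters mainly because the section does not correctly state what the trial was sized to show.

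**What to change.** The sponsor should retrieve the PASS inputs and output and correct the paragraph accordingly.

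- **If the non-inferiority basis is confirmed**, delete 40 vs 30% and write: *Assuming 30% ongoing pregnancy in both arms, a non-inferiority margin of 10 percentage points, one-sided alpha 0.025 and 80% power (score test), 329 evaluable women per arm are needed; 366 per arm allows for 10% loss.* The formula should be named, because the unpooled version gives 330 and would require 367 per arm. The reason for the margin belongs beside it.
- **If 40 vs 30% was intended**, keep the sentence but state the power as about 77% at 329 evaluable per arm (81% at 366 with no loss).

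The cost is a retrieved output file and a corrected, dated statement. Enrolment stays at 732 either way. In the second case the published power becomes slightly less favourable. The Trial Status section says recruitment is ongoing, so the correction is best made before outcomes are compared.

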#### Data Analysis

The intention-to-treat analysis will be used to examine differences in the ongoing pregnancy rate and other secondary outcomes in the two treatment arms during primary analysis. In addition, multiple imputations will be used to process missing values in the data. The demographic characteristics of the two groups will also be compared. Notably, categorical variables will be compared using χ2 analysis while the Student’s t-test will be used to compare quantitative variables. Moreover, multivariable logistic regression will be used to adjust for potentially confounding factors and results, if the randomization fails to achieve two balanced groups. Such factors will include the COH protocol, number of good-quality embryos, female age at oocyte-retrieval day, number of transferred embryos, retrieved oocytes, and quality of the transferred embryos. All statistical analyses will be performed using the SPSS version 26.0 software and a p-value <0.05 will be considered to be statistically significant.

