**Methods/analysis:**

The study is a randomized, non-inferiority, parallel-group, controlled trial that will enroll a total of 732 women undergoing their first FET after a failed fresh embryo transfer (ET) cycle. The participants will then be randomized into two groups based on a computer-generated randomized list. The two groups include: (i) an immediate group were FET will be carried out during the first menstrual cycle after a failed fresh ET cycle and (ii) a delayed group where FET will be carried out during the second menstrual cycle after a failed fresh ET cycle. Primary outcomes will be defined as viable pregnancies with fetal heartbeats, diagnosed through pelvic ultrasonography after twelve weeks of gestation.

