Presently, limited evidence exists on the “perfect” timing for FET following a failed-fresh stimulated IVF cycle. Notably, two options can be considered following a failed-fresh cycle: the first one would be to perform FET during the first cycle (an immediate embryo transfer) while the other option would be to postpone for least one menstrual cycle (a delayed embryo transfer). In addition, two studies on failed fresh IVF showed no differences in the live birth rates or clinical pregnancies between delayed and immediate FET (20, 21). In contrast, Mass K et al. suggested that patients should not postpone FET after fresh ET failure. Additionally, Volodarsky-Perel et al. reported that FET should be postponed for at least one menstrual cycle, after a failed-fresh cycle (17, 22). Therefore, given the contradictory reports, it is necessary to provide evidence-based randomized control guides for clinical practice. Consequently, the present randomized clinical trial aims to compare the ongoing pregnancy rate after immediate *versus* delayed FET following a failed-fresh cycle. It is hypothesized that the ongoing pregnancy rates of the two options will be comparable. The following article is presented in accordance to the SPIRIT reporting checklist.

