## Methods and Materials

### Study Design

The study is a controlled single-center, randomized, parallel group, non-inferiority clinical trial conducted at the Affiliated Hospital of Shandong University of Traditional Chinese Medicine (TCM). An overview of the study visits is shown in **Table 1**, and the study flow chart is highlighted in **Figure 1**.

**Table 1 T1:** Schedule of the study process (SPIRIT Figure).

	Study Period				
	Enrollment	Allocation	Post allocation		
Time point*	1st visit	2nd visit	3rd visit	Pregnancy visit	Follow-up visit
Preconception counselling	**√**	**√**	**√**	**√**	**√**
Eligibility screen	**√**				
Informed consent	**√**				
Questionnaire	**√**	**√**			
Laboratory index measurement (oocyte, zygote, embryo, *etc.*)	**√**				
Serological test for pregnancy		**√**	**√**	**√**	
Allocation (immediate FET or delayed FET)		**√**	**√**		
Menstrual cycle records			**√**		
Transvaginal ultrasound for pregnancy outcomes			**√**	**√**	**√**
Perinatal and neonatal outcomes records				**√**	**√**

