## Discussion

In daily clinical practice, deciding on when to perform FET after a failed oocyte retrieval-ET procedure is often a dilemma. In addition, most of the patients prefer to continue treatment by postponing the transfer of their remaining cryopreserved embryos.

In a small retrospective cohort study (n = 129), Volodarsky-Perel et al. found that postponing FET by at least one menstrual cycle after a failed fresh ET was beneficial for pregnancy outcomes compared to immediate FET. This was observed if a preceding long GnRH-agonist protocol for COS was used and if an artificial preparation was indicated for FET (22). However, these results were contrary to those recently reported by a large retrospective study (n = 1,183) which revealed a similar clinical pregnancy rate in first FET cycles that were performed immediately (≤22 days) or later on (>22 days) after oocyte retrieval from the preceding failed fresh ET (21). The study concluded that deferring FET may unnecessarily prolong the time to pregnancy. Nevertheless, the results were drawn from cycles that followed failed Fresh ET using the ovarian stimulation-GnRH-ant protocol. All in all, the contradictory results from the two studies may have been due to the different protocols used for ovarian stimulation, *i.e.* GnRH analog in the failed fresh ET and in the subsequent first FET cycle.

The purpose of this randomized controlled trial is not necessarily to confirm the superiority or inferiority of immediate FET after the failure of fresh ET. On the contrary, it aims to assure both clinicians and patients that although fresh ET fails, immediate FET has no adverse effects on the eventual pregnancy outcomes, compared to delayed FET. As such, it may be beneficial in alleviating psychological pressure on patients and shorten the Time to Pregnancy (TTP) and is therefore worth trying.

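### The trial is declared non-inferiority but states no margin or non-inferiority criterion; the only analysis and success rule given are for a difference test

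*Protocol article*

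**What the plan says.** The title, the abstract ("randomized, non-inferiority, parallel-group, controlled trial that will enroll a total of 732 women") and Study Design ("randomized, parallel group, non-inferiority clinical trial") all declare non-inferiority. The Introduction gives the hypothesis: "It is hypothesized that the ongoing pregnancy rates of the two options will be comparable". The Discussion says the aim is not necessarily to confirm superiority or inferiority, but to assure clinicians and patients that "immediate FET has no adverse effects on the eventual pregnancy outcomes, compared to delayed FET".

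The statistical sections use a different framework. Estimation of Sample Size gives 329 women per group for 80% power "to detect a minimally important absolute difference of 10% points between the immediate and delayed groups", illustrated as 40% against 30%, at two-sided alpha 0.05. This is raised to 366 per arm (732 in total) for 10% loss to follow-up. Data Analysis plans an intention-to-treat analysis of differences in ongoing pregnancy and the secondary outcomes. It then says "categorical variables will be compared using χ2 analysis", adds logistic regression if the groups are unbalanced, and closes with "a p-value <0.05 will be considered to be statistically significant" for all analyses.

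No section gives a non-inferiority margin, a null hypothesis tied to one, or a confidence limit to be judged against one.

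**The concern.** A chi-square test asks whether the data rule out equal rates. A non-inferiority claim needs the data to rule out a deficit as large as a stated margin. These are different questions: p≥0.05 can occur when the confidence interval still includes a large loss of pregnancies. Under the rule as written, a significant result shows only that the arms differ, and a non-significant result shows nothing about how much worse immediate FET might be. Neither outcome is tied to the conclusion that the trial was set up to reach.

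At stake is the primary conclusion. If the margin is left open until outcomes are known, any margin named then will lack credibility.

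**Working it through.** **Inputs.** From Estimation of Sample Size: 30% reference rate; 40% against 30%; 80% power; two-sided alpha 0.05; 329 per arm; 366 per arm after 10% loss. From Data Analysis: chi-square test, p<0.05. Assumed, because the article gives no value: a margin of 10 points, being the only candidate figure in the text, with other margins shown in step 5. Normal quantiles are 1.960 (97.5%) and 0.842 (80%); the square of their sum is 7.849.

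**1. The plan's figure by the method it describes.** Difference test with pooled variance under the null:

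n = [1.960·√(2·0.35·0.65) + 0.842·√(0.40·0.60 + 0.30·0.70)]² / 0.10² = 355.9, so 356 per arm.

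Other versions give 354 (unpooled), 356 (arcsine), 376 (continuity-corrected), 281 (one-sided) and 300 (one-sided, corrected). None gives 329. The power of the described test at 329 per arm is 76.8%.

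**2. The plan's figure as a non-inferiority calculation.** With 30% in both arms, a 10-point margin, one-sided 0.025 and 80% power:

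n = 7.849·(2·0.30·0.70) / 0.10² = 7.849·0.42 / 0.01 = 329.7.

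This matches 329 apart from rounding. Loss to follow-up: 329 / 0.90 = 365.6, so 366 per arm and 732 in total, which also matches.

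**3. Error rates of the two rules.** Exact binomial enumeration, delayed arm 30%. The chi-square column is the probability of p≥0.05. The interval rule claims non-inferiority if the lower two-sided 95% Wald limit for immediate minus delayed lies above −10 points.

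| True immediate rate | n per arm | p≥0.05 | Interval rule claims non-inferiority | p≥0.05 but interval rule fails |
|---|---|---|---|---|
| 20% | 329 | 15.5% | 2.5% | 13.0% |
| 20% | 366 | 11.9% | 2.5% | 9.4% |
| 25% | 329 | 70% | 30% | 40% |
| 25% | 366 | 67% | 33% | 34% |

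The 20% rows lie at the margin, so there a claim of non-inferiority is false. In the 25% rows the true deficit is inside the margin. Those rows show how often the two rules would give different messages; they are not false-claim rates.

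**4. One data set.** At 366 per arm, 88 against 110 ongoing pregnancies is 24.0% against 30.1%, a difference of −6.0 points. The pooled rate is 198/732 = 0.2705, its standard error √(2·0.2705·0.7295/366) = 0.0328, z = −1.83 and p = 0.067. The 95% interval is −6.0 ± 1.96·3.28, that is −12.4 to +0.4 points. The test is not significant, and a 10-point margin is not met.

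**5. Power if a margin is declared** (30% in both arms). Power = Φ(margin / √(0.42/n) − 1.96).

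| Margin | n per arm for 80% power | Power at 329 | Power at 366 |
|---|---|---|---|
| 10 points | 330 | 79.9% | 83.9% |
| 8 points | 516 | 61% | 66% |
| 7 points | 673 | 50% | 54% |
| 5 points | 1319 | 29% | 31% |

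**The case against.** Four points can be made for the plan.

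- **A margin was probably used.** Step 2 shows that 329 fits a 10-point margin and not the described difference test. A reader might infer that the trial was designed with no margin at all, and the arithmetic speaks against that. What stands is that the margin is undeclared and the text describes it as something else.
- **The article never says that p≥0.05 means immediate FET is not worse.** A reader might infer it from the comparability hypothesis and the reassurance aim, but it remains an inference. The supported statement is narrower: no other route to the intended conclusion is given.
- **The chi-square sentence follows one on demographic characteristics and may refer to baseline comparisons.** That reading is possible. Even so, chi-square is the only unadjusted test named for binary data, the primary analysis is worded as examining differences, and p<0.05 applies to all analyses.
- **A separate analysis plan may hold the confidence interval method.** Leaving that detail to another document would be normal. Here, however, the article states a framework and a criterion that do not fit its declared design, and an analysis plan that tested non-inferiority would conflict with that text.

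A reader might also take the 70% in step 3 as the rate of false reassurance. It is not: a 5-point deficit lies inside a 10-point margin, so under that margin immediate FET would be non-inferior.

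**Conclusion.** The concern holds. The declared design and the stated analysis do not match, and the stated criterion cannot support a non-inferiority conclusion. If non-significance were taken as reassurance, a true 10-point deficit would pass in 15.5% of trials at 329 per arm (11.9% at 366), against 2.5% under the interval rule. With a true 5-point deficit, about 40% (329) or 34% (366) of trials would be non-significant and yet fail a 10-point margin.

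These figures assume a 30% delayed rate, complete outcomes at the stated arm sizes and a 10-point margin. That the 10 points served as the margin is inferred from the reproduced sample size; the article does not say so. Nor does it justify 10 points as an acceptable loss, which against 30% is one third of ongoing pregnancies (10/30). The matter should be settled before outcomes are analysed, because the primary conclusion depends on it.

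**What to change.** Before outcomes are analysed:

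1. Declare the non-inferiority margin and justify it as an acceptable loss. Ten points is the only figure consistent with the planned 732 at 80% power and 30% in both arms. If a smaller margin is chosen, restate the power from step 5.
2. Rewrite Estimation of Sample Size as the non-inferiority calculation, with the assumed rate in both arms, the margin, one-sided 0.025 and 80% power. Remove the 40% against 30% wording, and align the Highlights sentence on detectable differences.
3. In Data Analysis, make the primary result the risk difference in ongoing pregnancy (immediate minus delayed) with a two-sided 95% confidence interval. Claim non-inferiority only if the lower limit lies above minus the margin.
4. Test superiority only after non-inferiority is shown, and state that p≥0.05 is not evidence of comparability.

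The cost is a documented protocol and analysis-plan amendment, with the registry entry brought into line. At a 10-point margin no extra patients or data are needed: power is about 80% at 329 per arm and 84% at 366. A smaller margin would mean more patients or an openly lower power.

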### Randomization

Women undergoing the first FET cycle after a failed-fresh cycle will be randomized into two groups (immediate and delayed) according to a computer-generated randomization list. Randomization will be conducted on the day of the negative blood *β*-hCG test (fourteen days after fresh embryo transfer), for participants with a failed-fresh ET. In addition, randomization will be conducted by the study nurse blinded from the entire recruitment and clinical management of the participants through random number generation and grouping using the SPSS software (Version 26.0, IBM Corp., Armonk). Moreover, the same project nurse will prepare the randomization arm by placing them into opaque envelopes for subsequent use. Finally, participants will be randomized according to the opaque envelopes into one of two groups: 1) The immediate group in which FET will be performed after the first menstrual cycle following the failed-fresh cycle; 2) The delayed group in which FET will be performed after two or more menstrual cycles following the failed-fresh cycle.

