### Interventions

Participants will undergo the IVF/ICSI treatment as clinically indicated. In addition, fixed GnRH antagonist (GnRH-ant) (cetrorelix; Merck Serono, Darmstadt, Germany) protocol will be employed with 150–450 IU/day of recombinant FSH (Puregon, MSD, Courbevoie, France; Gonal-F, Merck-Serono, Lyon, France). Additionally, the doses of gonadotropin will be determined based on the characteristics of individual patients. Thereafter, oocyte retrieval will be conducted under ultrasound transvaginal guidance, 34–36 h after triggering with GnRH-a (Triptoreline, Decapeptyl, Ipsen, France) or recombinant hCG (rhCG, Ovitrelle, Serono, France). Additionally, the BD Falcon IVF medium (Becton, Dickinson and Company, Franklin Lakes, NJ, USA) will be used to collect the oocytes and perform embryo culture at 6% CO_2_, 5% O_2_ and 37.0°C (C200 CO_2_ Incubator, Labotect Labor-Technik-Göttingen GmbH, Göttingen, Germany). After this, oocytes will be fertilized based on the semen quality of individual participants’ partner, using either conventional insemination or ICSI following the standard protocol. Normal fertilization will then be assessed (a second polar body and two pronuclei) after 16–18 h of insemination or ICSI. Notably, an embryo with at least seven blastomeres (grades one and two) on the third day after oocyte retrieval will be defined as good quality. In addition, embryos with fragments <50% will be frozen. According to the standard protocol, all “good” embryos will be vitrified using the cryopreservation method on the third day. Furthermore, patients with more than six good-quality embryos on the third day will be counseled for extended blastocyst and culture transfer.

In addition, a failed-fresh cycle will be defined as a negative *β*-hCG test, fourteen days after fresh embryo transfer. Participants will then be randomized to immediate *versus* delayed groups by specially assigned nurses on the material day. They will also be advised on whether to wait for one or more menstrual cycles after the failed embryo transfer, before the next visit. Moreover, all participants will receive the same treatment before and after the subsequent visit, and there will be no other relevant interventions or concomitant care during the clinical trial. The nurses will inform patients before enrollment that once they are assigned to a group, they will not be able to change unless an unexpected event necessitates the cancellation of embryo transfer.

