Furthermore, the participants’ stress and anxiety levels will be measured using a standard questionnaire before randomization and at the time of commencing FETs. In addition, the Chinese State-Trait Anxiety Inventory will be used to measure the patient’s anxiety levels (26).

On the other hand, Hormone Replacement Treatment (HRT) will be used for endometrial preparation. In addition, treatment with Estradiol valerate will commence on the third day of the menstrual cycle at a dose of 4–6 mg/day for 10–12 days. Moreover, vaginal progesterone (8% Crinone, Merck-Serono, Switzerland) will be administered at a dose of 90 mg per day, after the endometrial layer reaches a thickness of 8 mm as revealed by pelvic ultrasound scanning. FET for day three embryos will also be scheduled on the fourth day after commencing treatment with vaginal progesterone. Furthermore, at least one embryo with the best morphology, will be transferred using a soft embryo-transfer catheter with the guidance of ultrasound. Finally, the serum *β*-hCG levels will be checked fourteen days after FET.

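### The back-up adjusted model is triggered by chance imbalance and lists two covariates, number and quality of transferred embryos, that are settled only after randomisation

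*Protocol article*

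**What the plan says.** The Data Analysis section names an intention-to-treat comparison of ongoing pregnancy as the primary analysis, with χ² tests for categorical variables. It plans multiple imputation for missing values and says that "The demographic characteristics of the two groups will also be compared". It then adds that "multivariable logistic regression will be used to adjust for potentially confounding factors and results, if the randomization fails to achieve two balanced groups". No criterion for imbalance is given. Three of the listed factors are "number of transferred embryos, retrieved oocytes, and quality of the transferred embryos"; the other three are the stimulation protocol, the number of good-quality embryos and female age at retrieval.

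On timing, the Randomization section states that "Randomization will be conducted on the day of the negative blood" β-hCG test, fourteen days after fresh transfer. The Interventions section then describes endometrial preparation, after which "at least one embryo with the best morphology, will be transferred". The Data Entry and Quality Control section says that baseline and laboratory data are collected on the day of embryo freezing, whereas "data on the FET cycle will be collected on the day of frozen embryo transfer". The Blinding section says that participants and researchers cannot be blinded, but that the embryologist assessing embryo quality is.

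**The concern.** Two features of the conditional model are unsound.

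- **The trigger.** If the allocation procedure works, any imbalance between the arms is chance. Making adjustment depend on it lets the data choose the model. It also gives up the gain in precision from prognostic covariates such as age whenever the groups happen to look balanced.
- **Two of the covariates.** A variable settled after randomisation cannot confound a randomised comparison, but it can be a consequence of the allocation. Adjusting for it can then remove part of the effect under study or introduce bias. An imbalance in such a variable might itself be an effect of the arm, so the trigger could be set off by the very effect that the model then removes.

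The direction matters here. The trial is described as non-inferiority, and its Discussion says that it aims to reassure clinicians and patients that immediate transfer does no harm. Adjusting away a harm that acts through the transfer would favour that conclusion.

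**Working it through.** **Step 1. Place each listed factor in time.**

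| Factor | When settled | Relative to randomisation |
|---|---|---|
| Stimulation protocol | Fresh cycle | Before |
| Female age at retrieval | Retrieval day | Before |
| Oocytes retrieved | Retrieval day | Before |
| Number of good-quality embryos | Day-3 grading | Before |
| Number of transferred embryos | Frozen transfer; the text sets only a minimum of one | After |
| Quality of transferred embryos | Depends on which embryos are used at frozen transfer; most were graded and frozen earlier | Partly after |

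So two of the six factors are completed after open-label allocation. Number is the more exposed. Quality is partly protected because the assessor is blinded and most grading precedes allocation.

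**Step 2. Women without a transfer.** The Interventions section foresees cancellation of embryo transfer, and it starts progesterone only once the endometrium reaches 8 mm. For a woman with no transfer, embryo quality is undefined and the number transferred is zero or undefined. A model with these covariates must drop her or impute a value that never existed. The protocol gives no expected number of such women, so this cannot be sized.

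**Step 3. What adjustment can do to the estimate.** The documents give no data on how the arm might affect the transfer, so every input here is an assumption chosen to show the mechanism:

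- 60% of the delayed arm receive two embryos and the rest one;
- log-odds of pregnancy with one embryo −1.25; odds ratio for two versus one, 1.8;
- the arm has no other effect on pregnancy.

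Pregnancy probability with one embryo: 1/(1 + e^1.25) = 0.223.
With two: log-odds −1.25 + ln 1.8 = −0.662, giving 0.340.
Delayed arm: 0.60 × 0.340 + 0.40 × 0.223 = 0.293, close to the 30% that the protocol assumes.

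Now lower the log-odds of a two-embryo transfer in the immediate arm:

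| Shift in log-odds | Two-embryo share, immediate arm | Pregnancy rate, immediate arm | True difference |
|---|---|---|---|
| 0 | 60.0% | 29.3% | 0 |
| −0.6 | 45.2% | 27.6% | −1.7 points |
| −1.0 | 35.6% | 26.4% | −2.9 points |

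A simulation with 366 women per arm and 2,000 runs agrees. At a shift of −1.0, the unadjusted log odds ratio averages −0.147 (difference −2.9 points), while the model adjusted for number transferred averages −0.005. The true deficit disappears from the adjusted result. At a shift of 0, the two agree (−0.003 and −0.004) and there is no bias.

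**Step 4. The other mechanism.** Suppose an unmeasured prognostic factor influences both the number transferred and pregnancy (odds ratio 1.8 per standard deviation for pregnancy; log-odds 1.0 per standard deviation for number). The arm shifts number by −1.0, and number itself has no effect. The true arm effect is then zero. The unadjusted model rejects in 4.9% of runs. The adjusted model averages a log odds ratio of +0.094 and rejects in 8.3%.

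**The case against.** The strongest reply is that the primary analysis is already fixed. The intention-to-treat comparison is named as primary, needs no transfer covariates and can include every randomised woman; the regression reads as a conditional addition. This stands. A reader might infer that the primary intention-to-treat analysis is broken, or that the plan has two rival primary results, but the text supports neither. The problem is confined to the conditional model and to the weight it would carry.

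Second, the bias needs the arm to affect the transfer. The embryologist is blinded for the quality assessment, most embryos are graded and frozen before allocation, the best morphology is preferred, and the Interventions section promises the same treatment in both groups. This also stands and limits the claim to a possibility. It does not cover the number transferred, which is left open.

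Third, the phrase about transferred embryos could mean those of the fresh cycle, which would precede randomisation. The text does not say so, and the frozen transfer is the natural reading.

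Two further inferences are tempting but should not be drawn:

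- **A trigger probability.** Testing six factors at 5% gives 1 − 0.95^6 = 26.5%. But the protocol states no significance rule for imbalance, the embryo and oocyte counts are unlikely to be independent, and the count includes variables that are not baseline.
- **An error in listing the stimulation protocol.** All women follow a "fixed GnRH antagonist (GnRH-ant") protocol, so the factor may look constant. Dose, product and trigger agent vary, however, and a constant covariate would do no harm.

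**Conclusion.** The point holds for the adjusted model only. Its use depends on chance imbalance, and it includes two covariates completed after open-label randomisation that have no proper value for women without a transfer. The adjusted result can therefore be biased if the arm affects how many or which embryos are transferred; the unadjusted intention-to-treat result is not biased by this.

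The size cannot be fixed from the document. Over the assumed range, the deficit hidden by adjustment runs from nothing to about 2.9 percentage points, against the 10-point difference used in the sample size calculation. These figures illustrate a mechanism; they do not predict what will happen in this trial. The conclusion rests on reading transferred embryos as those of the frozen cycle. It is a change worth making, not a fault that undermines the trial.

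**What to change.** In the Data Analysis section:

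1. Delete the condition that adjustment follows only if the groups are unbalanced.
2. Remove number and quality of transferred embryos from the model and report both descriptively by arm, together with the number of women who had no transfer.
3. Always fit one pre-specified logistic model in all randomised women, with female age at retrieval, number of oocytes retrieved and number of good-quality embryos. All three are known before randomisation. Express the result as a standardised risk difference with its 95% confidence interval, beside the unadjusted difference.
4. State in advance which of the two risk differences carries the non-inferiority conclusion; the other is supportive. Without this step, always adjusting would itself leave two results with no declared order.

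The cost is revised wording and minor analysis work. The three covariates are already planned for collection, and no change to sample size or visits is needed.
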